#### 8. Amount of intraoperative fluid (crystalloid and colloid).

The volume of intraoperative fluids administered to study subjects will be reported.

#### 9. Amount of vasoactive medications (i.e. phenylephrine, ephedrine, nor-epinephrine, (1) epinephrine, dobutamine).

The type and amount of vasoactive medication administered to study subjects will be reported.

**10. Advanced hemodynamic variables at 20-sec intervals.**

**a. Hypotension prediction index (HPI).**

A descriptive summary of the HPI will be provided for study subjects.

**b. Cardiac output (CO).**

A descriptive summary of cardiac output will be summarized and provided for study subjects.

**c. Cardiac Index (CI).**

A summary of the cardiac index summarized and will be reported for study subjects.

**d. Stroke Volume (SV).**

The stroke volume will be summarized and reported for study subjects.

**e. Stroke Volume Index (SVI).**

The stroke volume will be summarized and provided for study subjects.

**f. Stroke Volume Variation (SVV).**

The stroke volume variation will be summarized and reported for study subjects.

**g. Dynamic arterial elastance (Eadyn).**

The Eadyn will be summarized and presented for study subjects.

**h. Maximal slope of the arterial pressure upstroke (dP/dt).**

The dP/dt will be summarized and reported for study subjects.

**i. MAP & PR .**

The mean arterial pressure and pulse rate will be summarized and reported for study subjects.

**11. Hospital length of stay.**

The length of stay in the hospital will be summarized and reported for study subjects.

**12. ICU Hospital length of stay.**

The length of stay in ICU will be summarized and reported for study subjects.

**13. Hospital readmission within 30 days.**

The percentage of study subjects with readmission to the hospital will be provided with the reasons for readmission.

**14. Cardiovascular mortality at 30 days.**

The percentage of study subjects who day within 30 days will be presented.

**15. Composite of systemic inflammatory response syndrome (SIRS) and at least one major organ dysfunction for renal, cardiovascular, respiratory, neurologic and coagulation systems by day 7 after surgery.**

The percentage of study subjects with this composite will be reported.

**16. Acute respiratory distress syndrome.**

The percentage of study subjects with acute respiratory distress syndrome will be reported.

**17. Acute pulmonary edema.**

The percentage of study subjects with acute pulmonary edema syndrome will be reported.

**18. Superficial or deep surgical site infection.**

The percentage of study subjects with surgical site infection will be reported.

**19. Hospital acquired infection.**

The percentage of study subjects with hospital acquired infection will be reported.

**20. Ventilator time.**

The ventilator time of study subjects will be summarized and presented.

## **VI. Multiplicity**

The testing for the primary effectiveness analysis will be a one-sided 0.025 test. The primary effectiveness analysis must meet its objective of statistical significance. After analysis of the primary effectiveness endpoint, if the primary analysis results in statistical significance, the descriptive secondary effectiveness endpoints will be presented with nominal two-sided 95% confidence intervals. Thus, the study will be protected from alpha inflation by the closed form hierarchical method. Multivariate analyses are considered supportive without control of alpha and the additional endpoint analyses are likewise supportive without control of alpha.

## **VII. Data Pooling**

Data from all study sites will be pooled for all analyses in this study based on the clinical criteria of Meinert (1986): all sites followed the same protocol, the sponsor monitored the sites for protocol compliance, and the data gathering mechanism was the same at each site. A sensitivity analysis will be done from the primary and secondary endpoints to determine if study site has an impact on the analysis endpoint.

## **VIII. Interim Analysis**

There will not be an interim analysis done in this study.

## **IX. Statistical Analyses**

### **A. Character of Study Variables**

As a routine evaluation of the data during analysis, consistency of the study variables to properties of statistical tests will be done. For continuous variables, equality of variance tests will be done to support analyses requiring this condition such as the Wilcoxon rank sum test. With categorical data, exact statistical test procedures will be to minimize test assumptions. For tabulated continuous variables, the descriptive analyses will present the mean, standard deviation, median, minimum and maximum. For tabulated categorical variables, the number with the characteristic, the total number evaluated, the percent and the 95% exact binomial confidence intervals will be provided.

### **B. Comparability Analyses of the Patient Populations**

These analyses are intended to determine the similarity of treatment groups and study sites with respect to important demographic or other variables, either known or suspected to have an influence on the outcome variables. The absence of similarity for any baseline variable will identify that variable as a potential covariate in subsequent safety and effectiveness multivariable analyses. The data for each baseline variable will be presented descriptively. For quantitative variables like age, the mean, standard deviation (SD), median, minimum, and maximum will be presented. For qualitative variables like gender, the number with the characteristic, the total number evaluated, the rate, and the exact 95% binomial confidence limits will be presented.

## 1. Comparability between Treatments

The comparison of baseline characteristics across treatment groups will apply the following methods. The quantitative variables such as age will be done with two-sided  $\alpha=0.05$  Wilcoxon rank sum test or two-sample t-test, and qualitative variables will be analyzed with Fisher's exact test or Fisher-Freeman-Halton test. Any variable found to have  $P<0.10$  will be used as a possible covariate in subsequent multivariate safety or effectiveness analyses.

## 2. Comparability between Study Sites

An analysis of comparability across study sites without regard to treatment assignment will be carried out by the same baseline characteristics by the analysis methods described above. Study site differences do not disallow pooling, but variables including study site and the variable found different need to be considered as covariates in subsequent multivariate analyses.

## C. Patient Accountability and Missing Data

A summary table will provide the total number of subjects enrolled and completed. The subjects eligible for and compliant with each follow-up contact will be summarized descriptively. Subjects withdrawn will be tabulated with their reasons for withdrawal.

Every effort will be made to collect all data points in the study. The sponsor plans to minimize the amount of missing data by appropriate management of the prospective clinical study, proper screening of study subjects, and training of participating investigators, monitors and study coordinators. The sponsor will provide a list of subjects who do not complete the trial along with the best information available on why they each left the trial prematurely.

While no imputation will be done for this study, sensitivity analysis by developing multivariate models of duration of IOH as a function of baseline and preoperative characteristics. If successful, the models may allow regression imputation for subjects with that are considered missing at random. Subjects with missing data that result from adverse events related to the test device or its use will be counted as not missing at random and will be imputed in the sensitivity analysis by random selection of a value with the same mean and SD as the untreated control distribution. Missing at random subjects will be imputed by random selection from a distribution with the same mean and SD as the treated subjects who have complete data.

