There are several sensitivity analyses to be done after the completion of the primary analysis. Assuming de-identified patient level data is available from MPOG, a multivariable mixed models analysis of variance will be done to determine if there are relevant impacts of patient characteristics that may impact the primary endpoint. Factors of concern will include gender, age, race, BMI, prior history of hypotension, prior history of heart disease, prior history of smoking, angiotensin receptor blockers, calcium channel blockers and ace inhibitors, ASA status, baseline MAP, history of coagulopathy, surgical time, intra-operative blood loss, diabetes, development of sepsis as an AE, chronic pulmonary disease and any baseline characteristic found out of balance by treatment group or study site. Factors will initially be screened with models that include treatment, the factor of interest, and the interaction between the two. Because of the increased power of the control sample, many of these comparisons could be statistically significant but not clinically significant. The screened factors will be evaluated to determine which should be included in a competition for the final model. This analysis will be done by backward elimination with no factors remaining in the final model with  $P > 0.05$ .

If it is not possible to get patient level data from MPOG, it may be possible for MPOG to perform the modeling by supplying them with the de-identified study data from our subjects.

From the model developed above, a second sensitivity analysis can be done to attempt to estimate the duration of IOH in subjects with missing data based on the model-based regression imputation (Little and Rubin, 2002). If a plausible model can be obtained, the imputation will be done with 10 different randomization seeds yielding ten populations from which a statistical test of the weighted site estimates can be used to provide supporting analysis to that done for the primary endpoint. The 10 imputed tests will be combined by the method of Rubin (1987) (this method is the substance of the SAS procedure MIANALYZE). The imputations will be done consistent with the guidance from the National Research Council Committee on National Statistics (2010).

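### The missing-data sensitivity analysis gives missing-at-random subjects two unranked imputation rules, one of which can only return the pooled complete-case mean in expectation

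*SAP*

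**What the plan says.** SAP section IX.C (Patient Accountability and Missing Data) opens its imputation paragraph with "While no imputation will be done for this study" and then describes a sensitivity analysis that does impute. It contains three rules.

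- **Missing at random, regression.** Models of IOH duration on baseline and preoperative characteristics are to be built and, if they succeed, "the models may allow regression imputation for subjects with that are considered missing at random".
- **Missing at random, marginal draw.** "Missing at random subjects will be imputed by random selection from a distribution with the same mean and SD" as the treated subjects with complete data.
- **Not missing at random.** The class is narrow: "Subjects with missing data that result from adverse events related to the test device or its use will be counted as not missing at random". These subjects receive "random selection of a value with the same mean and SD as the untreated control distribution".

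Section IX.D (Primary Effectiveness) returns to the regression method. If a plausible model is obtained, "the imputation will be done with 10 different randomization seeds yielding ten populations", and the ten tests are combined by Rubin's method. That model is the one built for the covariate sensitivity analysis. Its candidate factors include surgical time, intraoperative blood loss and sepsis arising as an adverse event. Building it needs patient-level registry (MPOG) data, or the registry's agreement to run the modelling itself.

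**The concern.** Two methods are given for the same subjects. Nothing says which one governs, whether one is the fallback, or what makes a model plausible enough to use. If the registry data do not arrive and the registry does not run the model, the marginal draw is the only missing-at-random rule left.

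That draw does not fit its label. Under missing at random, missingness may depend on observed characteristics, and the imputation has to condition on them. A draw that uses only the overall mean and SD of the complete treated subjects is justified only under missing completely at random. It puts the complete-case answer back into the data, so agreement with the primary result is built in and says nothing about robustness.

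Two smaller defects go with it. Section IX.C does not ask for repeated draws, and a single completed data set treats imputed values as observed. Both draws also fix only a mean and an SD, which does not determine a distribution for a skewed, non-negative quantity such as minutes of hypotension.

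**Working it through.** **Inputs from V.A.1 (Sample Size Computation).** Control mean 28.2 min, SD 42.5. Anticipated reduction 25%, so treated mean 0.75 × 28.2 = 21.15 and difference 7.05. Conservative SD-to-mean ratio 1.65, so treated SD 1.65 × 21.15 = 34.9. Completed subjects 389. Attrition 10% for surgery under three hours plus 4% lost to follow-up.

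**1. The plan's own figure.** The missing-data text states none. The related one is the attrition allowance: 389 / 0.86 = 452.3, which reproduces the SAP's 452. Four per cent of 452 is 18, so the working case is 389 observed plus 18 missing, 407 in all.

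**2. What the marginal draw returns.** With observed mean m and imputed values of expected mean m, the completed mean is (389m + 18m) / 407 = m. At m = 21.15 it stays at 21.15, and likewise for any missing fraction, when sites are pooled.

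**3. What it would miss.** The SAP gives no outcome for missing subjects, so their true mean is assumed to be the control mean (28.2) or twice it (56.4). True treated mean = (1 − f) × 21.15 + f × (mean in the missing):

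| Missing fraction f | Missing mean 28.2 | Missing mean 56.4 | After the marginal draw |
|---|---|---|---|
| 4% | 21.43 (24.0% reduction) | 22.56 (20.0%) | 21.15 (25%) |
| 10% | 21.86 (22.5%) | 24.68 (12.5%) | 21.15 (25%) |
| 14% | 22.14 (21.5%) | 26.09 (7.5%) | 21.15 (25%) |

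At 4% the undetected bias is 21.43 − 21.15 = 0.28 min to 22.56 − 21.15 = 1.41 min. The 10% and 14% rows are stress values: the planned 10% is an exclusion for short surgery, not missing data.

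**4. Simulation.** 20,000 runs, lognormal durations, 389 observed and 18 missing. The complete-case mean was 21.16 and was still 21.16 after the marginal draw. Control-distribution draws for all 18 gave 21.47. With the missing subjects truly at twice the control mean, the full-data mean was 22.72.

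**5. Standard error after one draw.** Treating 407 values as observed scales the complete-case standard error by √(389/407) = 0.978, a fall of 2.2%. The simulation gave 1.71 to 1.67, about 2.4%. Both ignore site weighting.

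**6. Site weighting.** The primary estimate weights site means by control proportions, and the draw is not site-specific. In an invented three-site example (control weights 0.5, 0.3, 0.2; observed 60, 150, 179; means 15, 21.15, 30; missing 9, 5, 4), pooled draws with mean 24.27 move the weighted mean from 19.85 to 20.46. That shift comes from pulling sites toward the pooled mean. It does not detect bias.

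**7. Shape.** If a normal distribution were used, the share of negative minutes would be Φ(−28.2/42.5) = 25% for control draws and Φ(−1/1.65) = 27% for treated draws. Setting negative control draws to zero would raise their mean from 28.2 to 34.7.

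**The case against.** The strongest reply is that no decision rests on these rules. Success is decided by the site-weighted t-test at one-sided 0.025, IX.C places the draws in a sensitivity analysis, and IX.D calls the imputed tests supportive. This stands: choosing between the rules after seeing the data cannot change the primary result.

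It can also be said that the rules do not truly conflict. Both regression statements are conditional, so the draw may be meant as the fallback, and the no-imputation statement can be read as covering the primary analysis only. Both readings are reasonable, but the SAP states neither. A fallback that is valid only under missing completely at random would still be a poor one.

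A reader might infer that the whole sensitivity analysis is incapable of revealing bias. The SAP does not support that. The control-distribution draw pulls the estimate toward no effect, the regression model in IX.D can move it where covariates predict both missingness and duration, and a further analysis in IX.D brings back patients with surgery under three hours.

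A reader might also take the negative-minutes problem as planned, or cost it at 4% × (34.7 − 28.2) = 0.3 min. The SAP never specifies a normal distribution. That sum applies the device-related rule to the entire loss to follow-up, and truncation at zero would in any case work against the device.

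**Conclusion.** The point holds as a minor one, confined to the missing-data sensitivity analysis. Missing-at-random subjects have two methods with no order between them. The marginal draw is valid only under missing completely at random, reproduces the pooled complete-case mean in expectation, cannot show bias among the subjects it covers, and slightly understates the standard error if done once (about 2% at 18 missing of 407).

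The likely size is small. At 4% missing the undetected bias is about 0.3 to 1.4 minutes against 7.05 planned, and this rests on assumed outcomes for the missing subjects. Even 4% may be too high: IOH is recorded during surgery, enrolment requires the arterial line and sensor to be connected, and the full analysis set needs only one postoperative assessment. Loss to 30-day follow-up need not make the duration missing.

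**What to change.** In IX.C:

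- State that the no-imputation statement refers to the primary analysis.
- Replace the marginal draw with multiple imputation (10 imputations, Rubin's rule), conditional on site and on baseline and preoperative covariates only. Exclude the surgical time, blood loss and sepsis factors listed in IX.D, which arise during or after surgery. Fit the model in the treated subjects, so that it does not depend on patient-level registry data and a method remains if those data are not released.
- For device-related missing values, draw within each of the 10 imputations from the observed control durations, or from percentiles supplied by the registry, by site where available. This settles the shape and excludes negative minutes.

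Align the imputation paragraph in IX.D with this, including the separate handling of device-related cases that it now omits.

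The cost is SAP wording, a little more analysis work and possibly a request to the registry for percentiles. The replacement still assumes missing at random given the covariates. A delta or tipping-point run on the same imputations would probe that assumption, but it goes beyond this point.

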## D. Primary Effectiveness

Recall that the study subjects were drawn from the same study sites that were used for the MPOG estimates from the control population. Because the sites may represent different patient populations, it is likely that the estimates from the site may be heterogeneous as were the estimates for the control MPOG sample. In an ideal world the proportion of subjects in the study will be similar to that from the MPOG controls, but the dynamics of study conduct usually result in a different subject distribution depending on which study sites were entered into the study earlier rather than later. In order to provide an estimate from the study sample that is most comparable to the controls adjusting for site the primary effectiveness endpoint will be done with a weighted average of site means and standard deviations as described below.

The study subjects will have the mean and standard deviation of the durations of IOH during the study computed by study site. To generate an estimate across the range of estimates for comparison to the MPOG controls, the estimates from each study site will be weighted and combined in the same proportion of subjects that were included in the control sample from MPOG. This method is analogous to direct standardization used in epidemiology (Fleiss et al (2003)). This weighted average and its properly computed standard deviation will be compared to the estimates obtained from MPOG by a one-sided unequal variance two-sample t-test. If this test is statistically significant with  $P<0.025$ , the primary effectiveness endpoint will be a success. If the proportion of subjects in the

control sample is  $p_k$  for study site  $k$  and the estimate of the mean from study site  $k$  is  $\bar{x}_k$ , then the study estimate from the interim sample for the overall mean is given below.

$$\bar{x} = \sum_k p_k \bar{x}_k.$$

If the standard deviation for study site  $k$  is  $s_k$ , then the estimate of the interim standard deviation is given below.

$$s = \sqrt{\sum_k (p_k s_k)^2}.$$

The test statistic for the interim is taken from the formula below.

$$t = \frac{\bar{x} - \bar{x}_{MPOG}}{\sqrt{\frac{s^2}{n} + \frac{s_{MPOG}^2}{n_{MPOG}}}}.$$

There are several sensitivity analyses to be done after the completion of the primary analysis. Assuming de-identified patient level data is available from MPOG, a multivariable mixed models analysis of variance will be done to determine if there are relevant impacts of patient characteristics that may impact the primary endpoint. Factors of concern will include gender, age, race, BMI, prior history of hypotension, prior history of heart disease, prior history of smoking, angiotensin receptor blockers, calcium channel blockers and ace inhibitors, ASA status, baseline MAP, history of coagulopathy, surgical time, intra-operative blood loss, diabetes, development of sepsis as an AE, chronic pulmonary disease and any baseline characteristic found out of balance by treatment group or study site. Factors will initially be screened with models that include treatment, the factor of interest, and the interaction between the two. Because of the increased power of the control sample, many of these comparisons could be statistically significant but not clinically significant. The screened factors will be evaluated to determine which should be included in a competition for the final model. This analysis will be done by backward elimination with no factors remaining in the final model with  $P > 0.05$ .

If it is not possible to get patient level data from MPOG, it may be possible for MPOG to perform the modeling by supplying them with the de-identified study data from our subjects.

From the model developed above, a second sensitivity analysis can be done to attempt to estimate the duration of IOH in subjects with missing data based on the model-based regression imputation (Little and Rubin, 2002). If a plausible model can be obtained, the imputation will be done with 10 different randomization seeds yielding ten populations from which a statistical test of the weighted site estimates can be used to provide supporting analysis to that done for the primary endpoint. The 10 imputed tests will be combined by the method of Rubin (1987) (this method is the substance of the SAS procedure MIANALYZE). The imputations will be done consistent with the guidance from the National Research Council Committee on National Statistics (2010).

Finally, a sensitivity analysis will be done on all patients regardless of the duration of surgery (including patients excluded from the primary endpoint analysis with less than three hours of surgery). The site averages and SDs will be combined by the method of weighting above and that mean and standard deviation will be compared to that from MPOG for all patients with at least 3 hours of surgery.

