### Additional Endpoints:

1. Reduction of IOH duration at MAP  $\leq$  60 mmHg;
2. Area under threshold MAP < 65 mmHg
3. Acute kidney injury (AKIN criteria);
4. Quality of recovery (QoR-15) on postoperative day 3;
5. Postoperative morbidity survey (POMS) on postoperative day 3;
6. Amount of red blood cells infused (ml packed red blood cells);
7. Amount of intraoperative fluid (crystalloid and colloid);
8. Amount of vasoactive medications (i.e. phenylephrine, ephedrine, nor-epinephrine, (1)epinephrine, dobutamine);
9. Advanced hemodynamic variables at 20-sec intervals:
  - a. Hypotension prediction index (HPI)
  - b. Cardiac output (CO);
  - c. Cardiac Index (CI);
  - d. Stroke Volume (SV)
  - e. Stroke Volume Index (SVI);
  - f. Stroke Volume Variation (SVV);
  - g. Dynamic arterial elastance (Edyn);
  - h. Maximal slope of the arterial pressure upstroke (dP/dt);
  - i. MAP & PR
10. Hospital length of stay;
11. ICU Hospital length of stay
12. Hospital readmission within 30 days;
13. Cardiovascular mortality at 30 days;

14. Composite of systemic inflammatory response syndrome (SIRS) and at least one major organ dysfunction for renal, cardiovascular, respiratory, neurologic and coagulation systems by day 7 after surgery (2);
15. Acute respiratory distress syndrome (3);
16. Acute pulmonary edema (3);
17. Superficial or deep surgical site infection (3);
18. Hospital acquired infection (4);
19. Ventilator time.

**Patient Population:** Subjects recruited and enrolled should be classified as American Society of Anesthesiologist (ASA) physical status 3-4 who are scheduled for moderate-to-high-risk non-cardiac surgery and will be receiving pressure monitoring with an arterial line. Potentially qualifying patients will be evaluated during their preoperative anesthesia clinic visits. ...

**Study Design:** A prospective, single-arm, open-label, multicenter post-approval study to determine whether the use of the Acumen™ HPI Feature Software to guide intraoperative hemodynamic management in non-cardiac surgery reduces the duration of intraoperative hypotension below a threshold of Mean Arterial Pressure (MAP).

**Number of Patients:** Up to 485 eligible subjects at up to 20 US study sites. The control group is comprised of 19446 patients. This number of controls is fixed and will not be altered.

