### **1. Sample Size Computation**

Recent analysis from the Multicenter Perioperative Outcome Group (MPOG) evaluated the mean duration of IOH in a subset of participating sites, during calendar year 2017, who met the eligibility criteria of this HPI Study. The analysis resulted in a total of 19446 patients with at least one minute of IOH and demonstrated a mean duration of IOH of 28.2 minutes with standard deviation 42.5.

It is anticipated that the HPI system will reduce that number of minutes by about 25%. Because the size of the standard deviation (SD) of the minutes in IOH decreases with decreasing mean. Estimates from other literature suggest that the SD is a similar fraction of the mean within the range. For this computation we assume that the ratio of the standard deviation to the mean remains constant. The ratio of the standard deviation of the mean from these data is  $42.5/28.2 = 1.50$ . To protect against the uncertainty of the ratio under powering the study, additional computations were done to make the estimate more conservative with a SD to mean ratio of 1.65. The minimum recommended required sample size, using Pass 14, of 389 completed subjects for 90% power for a one-sided  $\alpha = 0.025$  test which were derived from the additional computations of standard deviation ratios. Assuming an attrition for a less than 3-hour surgery of 10% and a small loss to follow-up of 4%, the recruited sample size should be  $389/0.86 \approx 452$  for 90% power in the Pivotal cohort. Therefore, the sample size for this study will be capped at 485, including up to 33 roll-in subjects and up to 452 Pivotal subjects, for a minimum of 90% power. Roll-in subjects will be analyzed separately from Pivotal subjects.

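### The primary test standardises the small HPI group to the registry's site mix; once the variance is computed correctly this may take power below 90%, and standardising the controls instead avoids nearly all of the loss

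*SAP*

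**What the plan says.** SAP section IX.D (Primary Effectiveness) computes a mean and SD of hypotension duration at each study site for the HPI subjects. It then states that "the estimates from each study site will be weighted and combined in the same proportion of subjects that were included in the control sample". The weighted HPI mean is compared with the unadjusted MPOG mean by a one-sided unequal-variance t-test. The same section expects the two site mixes to differ: "the dynamics of study conduct usually result in a different subject distribution".

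The section asks that the SD of the weighted average be computed properly. The formula it prints is s = √Σ(p_k s_k)², and s² is then divided by the total n. The site sample sizes n_k do not appear.

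Section V.A.1 (Sample Size Computation) asks for "389 completed subjects for 90% power for a one-sided" α of 0.025 and caps enrolment at 452 Pivotal subjects "for a minimum of 90% power". It does not mention the site weighting. No section sets a minimum enrolment per site or says what happens at a control site with one or no analysed HPI subject.

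**The concern.** Direct standardisation can run in either direction: HPI subjects to the registry mix, or controls to the HPI mix. Both remove the imbalance in site mix. They differ in which group bears the variance cost of unequal weights, and the plan places it on the group that is about 50 times smaller (19446/389).

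With a correct variance, a large registry site that enrols few HPI subjects gets a large weight on a poorly estimated mean. A handful of patients could then largely decide the primary result, and the planned power need not hold. A site with exactly one analysed HPI subject has no SD, so the planned SD could not be computed at all.

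**Working it through.** **Inputs from the SAP**
- Test: "The testing for the primary effectiveness analysis will be a one-sided 0.025 test" (VI).
- Controls: "The control group is comprised of 19446 patients" (Analysis Summary); the registry data "demonstrated a mean duration of IOH of 28.2 minutes with standard deviation 42.5" (V.A.1).
- Effect: a reduction of about 25% (V.A.1), so 28.2 → 21.15 min, difference d = 7.05 min.
- Treated SD: the stated conservative SD-to-mean ratio of 1.65 gives 1.65 × 21.15 = 34.9.
- Not given: the site shares p_k and q_k. All site shares below are assumptions.

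**Step 1. Reproduce 389 (unweighted, normal approximation)**

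n = SD_T² / [(d/3.2416)² − SD_C²/19446], where 3.2416 = 1.960 + 1.2816.

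(7.05/3.2416)² = 4.730 and 42.5²/19446 = 0.0929, so the denominator is 4.637.
- SD_T = 42.5: 1806.25/4.637 gives n = 390, and power at 389 is 0.8996. This reproduces the plan's figure.
- SD_T = 34.9: 1217.8/4.637 gives n = 263, and power at 389 is 0.975.

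The 389 therefore corresponds to SD 42.5 in both groups, not to the described ratio applied to the reduced mean. Both SDs are carried forward.

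**Step 2. Correct variance under the planned weighting**

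Var(Σ p_k x̄_k) = Σ p_k² s_k²/n_k. With a common SD and n_k = n q_k this equals F × SD_T²/n, where F = Σ p_k²/q_k ≥ 1, with equality only if the mixes match.

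Power = Φ(7.05/√(F × SD_T²/389 + 0.0929) − 1.96), where SD_T²/389 is 3.131 (SD 34.9) or 4.643 (SD 42.5).

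| F | Power, SD 34.9 | Power, SD 42.5 |
|---|---|---|
| 1 | 97.5% | 90.0% |
| 1.25 | 94% | 83% |
| 1.5 | 90% (89.6) | 76% |
| 2 | 80% | 63% |

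The largest F that keeps 90% power is 4.637/3.131 = 1.48 for SD 34.9 and 4.637/4.643 = 1.00 for SD 42.5.

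**Step 3. An assumed mismatch**

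One site holds 20% of controls and 2% of HPI subjects (about 8 of 389); the other sites keep their relative shares.
- F = 0.2²/0.02 + 0.8²/0.98 = 2.000 + 0.653 = 2.653. That one site carries 2.000/2.653 = 75% of the HPI variance.
- SD 34.9: SE = √(3.131 × 2.653 + 0.0929) = 2.90, power 68%.
- SD 42.5: SE = √(4.643 × 2.653 + 0.0929) = 3.52, power 52%.

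**Step 4. Same case with the controls standardised to the HPI mix**

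The factor F′ = Σ q_k²/p_k now multiplies only 0.0929. Here F′ = 0.02²/0.2 + 0.98²/0.8 = 1.2025.
- SD 34.9: SE = √(3.131 + 0.0929 × 1.2025) = 1.80, power 97.5%.
- SD 42.5: SE = √(4.643 + 0.0929 × 1.2025) = 2.18, power 90%.

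Even at F′ = 5, power is 96.1% and 87.7%, a loss of at most about 2.3 points.

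**Step 5. How far the result depends on the assumed shares**

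Site shares for both groups were drawn at random (Dirichlet).
- Concentration 5: median F was 1.37 with 10 sites and 1.43 with 20; 33% and 39% of draws exceeded 1.48.
- Concentration 2: medians were 2.12 and 2.35; 88% and 98% of draws exceeded 1.48.

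**Step 6. The formula as printed**

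With ten equal, perfectly matched sites, Σ p_k² = 0.1. At SD 34.9 the printed SE is √(0.1 × 3.131 + 0.0929) = 0.64 against a true 1.80, so the one-sided type I error is Φ(−1.96 × 0.637/1.795) ≈ 0.24 rather than 0.025. In the Step 3 case, with the other nine sites taken as equal, the printed SE is 0.66 against 2.90, and the type I error is about 0.33.

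**The case against.** A reader might infer that the test as written loses its 90% power. The SAP does not support that, for two reasons. The printed standard error contains no n_k, so an under-enrolled site cannot enlarge it; as printed, the harm is false positives, not lost power. And the SAP gives neither set of site shares. With matched mixes nothing is lost, and with moderate mismatch at SD 34.9 most of the random draws above kept 90%. Both points stand. The power argument applies only once the variance is put right, as the section's own call for a proper SD requires, and it is conditional on the mismatch.

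The reserve is also open to argument. SD 34.9 is not the input that yields 389, so 97.5% is not the plan's operating point; at SD 42.5 there is no reserve at all. In the other direction, the full analysis set (IV.B) does not require 30-day completion. At the cap, n could be about 452 × 0.90 = 407, which moves the SD 34.9 threshold to about 1.48 × 407/389 = 1.55.

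The strongest defence is that direction is partly a choice of target. The plan aims at the fixed registry mix and keeps 28.2 min as comparator. Standardising the controls makes both depend on enrolment, and if the effect varies by site the two directions estimate different quantities. This is a real cost and must be stated. It does not outweigh the efficiency gain, because the section's stated purpose is a site-adjusted comparison with the controls, and either direction provides one.

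**Conclusion.** This is a cheap improvement worth making, conditional on first correcting the variance to Σ p_k² s_k²/n_k. The plan puts the cost of unequal site weights on the small group, expects the mismatch that causes the cost, and makes no allowance for it in the sample size.

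Power may fall below 90%; that it will is not shown. At n = 389 it does so above a factor of about 1.48 if the treated SD is 34.9, and with any mismatch if it is 42.5. The 68% and 52% figures rest on an assumed 20%/2% split at one site, a common SD across sites and a normal approximation. Moving the weights to the controls gives the same site balance, at a cost of about two points at most in the range examined.

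**What to change.** First, in IX.D, replace the printed SD with a variance that uses site sample sizes: Σ p_k² s_k²/n_k.

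Then make the primary comparison the simple mean of the HPI subjects (variance s_T²/n_T, or the pooled within-site variance) against the control mean standardised to the HPI site mix. That control mean is Σ q_k × (control mean at site k), with variance Σ q_k² s_Ck²/N_k and q_k = n_k/n. Keep the one-sided unequal-variance test at 0.025.

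State that the target is now the enrolled site mix and that the comparator is no longer exactly 28.2 min. Keep the present direction as a sensitivity analysis, with the correct variance and a rule for sites with one or no HPI subjects. Carry the change into the other IX.D analyses that reuse the weighting: the tests on imputed data and the analysis regardless of surgery duration.

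If the present direction is kept as primary, add the sparse-site rule and a sample-size allowance for the weighting. In either case, state in V.A.1 which SD produced 389.

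Cost: SAP wording plus site-level means, SDs and counts from MPOG. Section II describes the control data as patient-level. Section IX.D is less sure that such data will reach the sponsor, but site summaries are enough. The 19446 controls stay fixed.
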